**2.1 Co-primary objectives**

This study has four main objectives

- Identification of a drug that could be used safely and effectively for IPTi instead of SP in areas, such as north eastern Tanzania, where there are high levels of resistance to SP and amodiaquine.
- Determination of whether a short acting antimalarial drug (Lapdap) is as effective as a long acting drug (mefloquine) when used for IPTi.
- Investigation of the effect of the intensity of transmission on the requirements for a long or short acting drug for IPTi.
- Assessment of the effect of IPTi on the development of clinical immunity in children in low and high transmission areas.

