**5. Monitoring of the trial**

The trial will be conducted under conditions of good clinical practice (GCP), following as closely as possible the ICH guidelines. Standard operating procedures (SOPs) will be developed for all major operations. A DSMB will be established to look after the trial. Members will include an experienced clinician, a statistician and a person with local knowledge of the study area. Discussions will be held with the DSMB prior to the start of the trial to identify their requirements for adverse events reporting and these will be met. The DSMB will also be consulted about the advisability of an interim analysis, in particular for the SP group as this drug may prove to be ineffective.

At each study site, a local physician will be assigned to be the local safety monitor. He or she will have access to the codes of the study drugs. All serious adverse events will be reported to the local safety monitor by the project physician. In the event of a serious adverse event associated with a study drug, the local safety monitor will be empowered to break the code for that child and, if it is considered necessary to temporarily suspend the trial, prior to discussion with the DSMB.

It is proposed that a clinical monitor will be appointed by the IPTi consortium to monitor all the trials conducted under its auspices and it is anticipated that the monitor will visit the study site on at least one occasion during the trial and provide advice that will help to ensure that the study is conducted to the highest clinical standard.

1. **Data management and analysis**

Data will be entered twice into a database using access software. The accuracy of data input will be checked and validated using a customized validation programme. The comparison of the incidence of malaria and severe malaria will be analysed using Poisson regression models. The statistical significance of differences in mean Hb will be assessed using t-test. We will consider the trials in the low and high transmission areas as separate and we recognise that trials is not adequately powered to make a direct comparison of the effects in the two areas.

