There will be two comparisons which are relevant with respect to multiple comparison, Lapdap vs Placebo and SP vs Placebo, and Mefloquine vs placebo will be the primary comparison. As we expect the effects of the two drugs to be similar, it would not be appropriate to power the trial on the Lapdap vs SP comparison. If we make two comparisons at the .025 level of significance then, under the null hypothesis, there is a .05 probability that one will be significant by chance. However we argue it would be appropriate to conduct one-sided tests, on the basis that there is no mechanism by which those given the active drug would have more malaria in the first year than those who do not.

We considered the possibility of powering the study at the 0.025 significance level rather than 0.05 level to allow for an excess of malaria in the first year of life among those on the active drugs in order to get over issue of the multiple comparisons. This would require increasing the sample size by 20%. This would mean increasing the number of infants in the low transmission are from 2200 to 2600 and in the high transmission areas from 1200 to 1440. This would require prolonging the study by four months. Thus,

we have opted to keep the power of the study at 0.05 level for the following reasons: (1) an enhanced incidence of malaria during the first year of life while on an active drug is very unlikely and so we can use a one-sided test (2) enrolling an additional 640 infants would increase substantially the logistical complexity and cost of the study but the added value of this would be small.

A detailed analytical plan will be prepared and submitted to the DSMB before the study drug codes are broken.

1. **Dissemination of results**

The nature of the trial and its possible implications will be discussed with the national Malaria Control and EPI programmes before the start of the trial. On completion of the study, results will be presented to the communities where the trial was undertaken, to local health authorities and to the National Malaria Control programme as well as in the international scientific press.

1. **Ethical considerations**

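### Lapdap versus mefloquine, a co-primary 'as effective as' question, is unnamed in Section 6 and sized only for superiority, and co-primary objective 3 has no between-site contrast

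*Protocol*

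**What the plan says.** Section 2.1 lists four co-primary objectives. The second is: "Determination of whether a short acting antimalarial drug (Lapdap) is as effective as a long acting drug (mefloquine) when used for IPTi". The third is: "Investigation of the effect of the intensity of transmission on the requirements for a long or short acting drug for IPTi".

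Section 6 (Data management and analysis) states the model for malaria incidence: "The comparison of the incidence of malaria and severe malaria will be analysed using Poisson regression models". On comparisons it says "Mefloquine vs placebo will be the primary comparison", and of the other two drugs: "There will be two comparisons which are relevant with respect to multiple comparison, Lapdap vs Placebo and SP vs Placebo". Lapdap versus SP is mentioned only to say that the trial should not be powered on it. Lapdap versus mefloquine is not mentioned.

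On the sites, Section 6 treats the two areas as separate trials and concedes that the "trials is not adequately powered to make a direct comparison of the effects in the two areas".

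The Lapdap–mefloquine contrast does appear in Section 4.4. Tables 6a and 6b have a column for it (393 and 262 per arm for clinical malaria), and the text claims 90% power for a 0.5 g/dl haemoglobin difference between those arms. The stated assumption is that Lapdap has half of mefloquine's effect. No equivalence or non-inferiority margin is given anywhere. In Section 4.12 transmission level enters only as a covariate in the antibody and immunity model.

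**The concern.** An 'as effective as' question needs a stated margin. Without one, a superiority test can answer no, but its failure to reach significance cannot be read as yes. The protocol recognises the distinction elsewhere: Appendix 2 calls the proposed two- versus three-course comparison an equivalence study. A positive answer also matters to the authors, because Section 1.4 makes the suitability of a Lapdap–artesunate combination conditional on short-acting drugs being shown to match long-acting ones.

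Objective 3 asks whether the Lapdap–mefloquine difference changes with transmission. Section 3.1 moved a whole site to keep a true high-transmission area for the between-area question. With two separate analyses and no joint estimate, the report would have no planned quantity that addresses it.

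**Working it through.** **Inputs.** Clinical malaria per child-year, Tables 6a and 6b: low site placebo 0.40, mefloquine 0.20, Lapdap 0.30; high site 0.62, 0.30, 0.45. Infants per arm, Section 4.4: 610 and 320; after 10% loss, 610 × 0.9 = 549 and 320 × 0.9 = 288.

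**1. Reproduce the plan's sizes.** n = (1.96 + 0.84)² × (r1 + r2)/(r1 − r2)², with (1.96 + 0.84)² = 7.849 unrounded.
- Low: 7.849 × 0.50/0.10² = 392.4, so 393 (stated 393).
- High: 7.849 × 0.75/0.15² = 261.6, so 262 (stated 262).

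A one-sided 5% test would give 309.1 and 206.1, which do not match. The plan's sizes are two-sided superiority sizes.

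**2. What the planned sample can show.** Superiority power = Φ(|r1 − r2|/√((r1 + r2)/PY) − 1.96).
- One person-year per infant: low Φ(0.10/√(0.50/549) − 1.96) = 91%; high Φ(0.15/√(0.75/288) − 1.96) = 84%.
- At 0.75 person-year per infant: 82% and 72%.

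**3. What a positive conclusion would need.** The margins are assumptions, expressed as the share of the mefloquine–placebo rate difference that may be lost. True rates are taken as equal, with one-sided 2.5% (the upper limit of a two-sided 95% CI) and one person-year per infant. On the difference scale, power = Φ(margin/√(2 × r_MQ/PY) − 1.96). The standard errors are √(0.40/549) = 0.0270 and √(0.60/288) = 0.0456.

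| Share lost | Margin low / high | Power low / high | At 0.75 person-year |
|---|---|---|---|
| 50% | 0.10 / 0.16 | 96% / 94% | 89% / 86% |
| 33% | 0.066 / 0.106 | 69% / 64% | 56% / 52% |
| 25% | 0.05 / 0.08 | 46% / 42% | 36% / 33% |

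If Lapdap is as weak as Table 6 assumes, the chance of declaring it as effective is at most 4% for each of these margins.

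**4. The same margins as rate ratios.** Poisson regression gives a rate ratio, and power is lower on that scale. SE(log RR) = √(2/(r_MQ × PY)): √(2/(0.20 × 549)) = 0.135 and √(2/(0.30 × 288)) = 0.152. A 50% loss is RR 0.30/0.20 = 1.50 (low) and 0.46/0.30 = 1.53 (high), with power Φ(ln 1.50/0.135 − 1.96) = 85% and Φ(ln 1.533/0.152 − 1.96) = 80%. A 33% loss (RR 1.33 and 1.352) gives 56% and 51%. A 25% loss (1.25 and 1.267) gives 38% and 34%. The choice of scale therefore has to be fixed with the margin.

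**5. Objective 3.** The planned Lapdap/mefloquine ratio is 0.30/0.20 = 1.5 at the low site and 0.45/0.30 = 1.5 at the high site, so on the Poisson scale the planning figures contain no interaction. With 10 months' follow-up (the endpoint covers 2–11 months), person-years are 549 × 10/12 = 457.5 and 288 × 10/12 = 240. The SE of the log ratio of rate ratios is √(1/(0.20 × 457.5) + 1/(0.30 × 457.5) + 1/(0.30 × 240) + 1/(0.45 × 240)) = 0.203. The 95% factor is exp(1.96 × 0.203) = 1.49 either way.

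**The case against.** The contrast is plainly intended. It has its own column in both sample-size tables, the planned numbers exceed what that column needs, and the haemoglobin statement names the two arms. The Section 6 list is introduced as the comparisons that matter for multiplicity, and the general Poisson sentence could cover any pair. Superiority also fits the authors' expectation that Lapdap will do worse. The between-site power limit is openly admitted, and a detailed analysis plan is promised before the codes are broken.

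Most of this stands, and it rules out stronger readings that a reader might infer:
- That the trial can only say whether each drug beats placebo. Section 4.4 supports a conclusion that Lapdap is worse than mefloquine.
- That the one-sided argument is misapplied to this contrast. The rationale, "there is no mechanism by which those given the active drug would have more malaria in the first year", is made for active drug against no active drug and is never extended to two active drugs.
- That the weakness on objective 3 is hidden. It is stated.
- That 1.5 can be taken from Table 6 as a margin. It is the ratio at which the protocol has Lapdap losing about half of mefloquine's benefit, so passing it could accept almost the inferiority that is predicted.

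The promised plan does not dispose of the point. The hypothesis type and margin determine what the sample can answer, and this document already fixes the primary comparison and the separate-trial approach.

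**Conclusion.** The point holds in this limited form. Objective 2 can be answered no with good power (about 91% and 84% at planned rates and one person-year per infant), but as written it has no route to yes. Objective 3 remains co-primary with no contrast planned and with planning figures that assume equal rate ratios at the two sites.

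Whether the existing sample could support a positive conclusion depends on the margin. Power is fair to good if half of mefloquine's effect may be lost (96%/94% on the difference scale, 85%/80% on the ratio scale) and poor for a quarter (46%/42% and 38%/34%). These figures rest on Table 6 rates, equal true rates, 10% loss and assumed margins. They fall with shorter follow-up. They also fall if malaria is rarer at the low site than planned, which Section 4.5 suggests when it ends scheduled visits there at 18 months because incidence is low.

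**What to change.** In Section 6:
- Name Lapdap versus mefloquine at each site, reported as a rate ratio with a two-sided 95% CI.
- Allow a conclusion that Lapdap is as effective only if the upper limit lies below a margin that is justified and fixed, with its scale, before unblinding. State the resulting power. Do not adopt 1.5 as though Table 6 supplied it.
- If no defensible margin is achievable with this sample, reword objective 2 as estimation of the difference between the two drugs.
- For objective 3, add one pooled Poisson model with site, drug and site × drug. Report the ratio of rate ratios with its CI (a factor of about 1.5 either way at planned rates and 10 months' follow-up) and label the objective as estimation.

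The cost is some protocol wording, one extra model and the effort of agreeing a margin. No more infants are needed.

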**9. Budget**

The details of the budget are shown in Table 8.

**Equipments:** one four wheel drive vehicle is needed in each site for day to day running of the project at EPI clinics. An additional vehicle is needed for the co-ordinating team. Six motor bikes are needed in each site for home visits for delivering drugs, monitoring adverse events and follow up of defaulters. Two computers are needed in each site for double entry of data and one computer is needed for the central office. Three study health facilities do not have a microscope at the moment and two more microscopes are needed for examining slides at the central point for quality control. All study health centres (12) need a haemacue machine and an additional 2 machines are needed for use during home visits. One digital camera per site is needed for making photo ID cards for study children. Two centrifuges (one for each site) for the separation of plasma and blood cells, two -20 freezers and 7600 eppendorf tubes will be need for the immunology component of the study.

**Personnel**: The project director will be a LSHTM member of staff based in Tanzania. An experienced research fellow is needed for this position in order to ensure a high standard of conduct of the trial. One project physician is needed for each site for running the project and to give clinical support to the health centre staff. Two project nurses and ten field assistants per site are needed for running the EPI clinics and for following up of study children at homes. Two data entry clerks and one data manager per site are needed as the data will entered daily and the list of study infants due for follow up has to be generated every week. The clinical officers at the study health centres will play an important role in passive surveillance. Two laboratory technician will be needed in each site for processing and storage of blood samples.

**Consumables:** The laboratory consumables are estimated on the basis of our experience in an IPTi trial in Ghana.

**Travel and subsistence**: This budget is needed for the LSHTM based PIs and the local PIs and collaborators to visit the study site for monitoring progress of the study and to ensure the high standard of the trial. The budget for post graduate training for the Tanzanian staff is essential for capacity building at the NIMR of Tanzania.

**LSHTM inputs**: The LSHTM will contribute in the order of $ 50,000 per year [ [name] (10%), [name] (10%), [name] (10%) and [name] (5%)].

Table 8

| **Budget estimates for the two sites** | |  |  |  |  |  |
| --- | --- | --- | --- | --- | --- | --- |
| **Items** | | **units** | **unit cost($)** | **total cost ($)** |  |  |
| **Capital** |  |  | year 1 | year 2 | year 3 | total |
| 4 wheel drive vehicle | 3 | 30000 | 90000 |  |  | 90000 |
| motor bikes | 12 | 6000 | 72000 |  |  | 72000 |
| computers | 5 | 2000 | 10000 |  |  | 10000 |
| printers | 2 | 300 | 800 |  |  | 800 |
| microscope | 5 | 2000 | 10000 |  |  | 10000 |
| Haemacue machines | 14 | 1000 | 14000 |  |  | 14000 |
| electonic thermometers | 14 | 20 | 280 |  |  | 280 |
| digital camera | 2 | 500 | 1000 |  |  | 1000 |
| **subtotal** |  |  | **198080** |  |  | **198080** |
|  |  |  |  |  |  | 0 |
| **Personnel** |  | cost per month |  |  |  | 0 |
| project director | 1 | 7000 | 84000 | 88200 | 92610 | 264810 |
| project physicians | 2 | 3000 | 36000 | 37800 | 39690 | 113490 |
| project nurses | 4 | 1200 | 14400 | 15120 | 15876 | 45396 |
| Field assistants | 20 | 4000 | 48000 | 50400 | 52920 | 151320 |
| laboratory technicians | 4 | 1200 | 14400 | 15120 | 15876 | 45396 |
| data managers | 2 | 1200 | 14400 | 15120 | 15876 | 45396 |
| data entry clerks | 4 | 800 | 9600 | 10080 | 10584 | 30264 |
| drivers | 3 | 600 | 7200 | 7560 | 7938 | 22698 |
| clinical officers (honororium) | 10 | 2000 | 24000 | 24000 | 24000 | 74000 |
| local safety monitor | 2 | 100 | 2400 | 2400 | 2400 | 7400 |
| local PIs & collaborators (honororium) |  |  | 8000 | 8000 | 8000 | 24000 |
| Lead PIs salary (20%) |  |  | 16000 | 18000 | 20000 | 54000 |
| **subtotal** |  |  | **278400** | **291800** | **305770** | **875970** |
|  |  |  |  |  |  |  |
| **consumables** |  |  |  |  |  |  |
| microcuvettes (100 per box) | 200 | 40000 | 10000 | 20000 | 10000 | 40000 |
| lancets (100 per box) | 400 | 4000 | 1000 | 2000 | 1000 | 4000 |
| glass slides (50 per box) | 400 | 2000 | 500 | 1000 | 500 | 2000 |
| filter papers (boxes of filter mats) | 5 | 1000 | 1000 | 0 | 0 | 1000 |
| stains and lab consumables |  |  | 1000 | 1000 | 1000 | 3000 |
| stationary |  |  | 3000 | 2000 | 2000 | 7000 |
| drugs |  |  | 20000 | 5000 | 5000 | 30000 |
| lab charges for HPLC & SSOP |  |  |  |  | 10000 | 10000 |
| lab charges for ferritin assays |  |  |  |  | 10000 | 10000 |
| lamination of idcards |  |  | 2000 | 2000 | 1000 | 5000 |
| fuel & maintanence of vehicles |  |  | 35000 | 35000 | 35000 | 105000 |
| **subtotal** |  |  | **71500** | **66000** | **64500** | **202000** |
| **travel and subsistance & capacity building** |  |  |  |  |  |  |
| international travel |  |  | 10000 | 5000 | 10000 | 25000 |
| local travel |  |  | 5000 | 2000 | 2000 | 9000 |
| post graduate training for staff |  |  |  | 20000 | 20000 | 40000 |
| **subtotal** |  |  | **15000** | **27000** | **32000** | **74000** |
| **admistration** |  |  |  |  |  |  |
| office rents & communication |  |  | 8000 | 8500 | 9000 | 25500 |
| Research permits and bank charges |  |  | 3000 | 1000 | 1000 | 5000 |
| local collaborators' admin cost |  |  | 14400 | 15900 | 16000 | 46300 |
| **subtotal** |  |  | **25400** | **25400** | **26000** | **76800** |
| **overheads (10% of non-capital expenses)** |  |  | **38490** | **39130** | **41827** | **119447** |
| **grand total** |  |  | **621870** | **404976** | **449330** | **1551297** |

**10. Timetable**

The time schedule of key activities is shown in Table 9.

**Table 9**: **Time Table of activities**

|  | Year 1 (July 2004-June 2005) | | | | Year 2(July 2005- June 2006) | | | | Year 3(July 2006-June 2007) | | | |
| --- | --- | --- | --- | --- | --- | --- | --- | --- | --- | --- | --- | --- |
| Activities | Q1 | Q2 | Q3 | Q4 | Q1 | Q2 | Q3 | Q4 | Q1 | Q2 | Q3 | Q4 |
| Recruitment of staff and preparation of logistics & supplies | X |  |  |  |  |  |  |  |  |  |  |  |
| Sensitisation of the community and launch of the study | X |  |  |  |  |  |  |  |  |  |  |  |
| Enrolment of subjects for the drug sensitivity study |  |  |  |  |  | X |  |  |  |  |  |  |
| Follow up of subjects enrolled in the drug sensitivity study |  |  |  |  |  | X |  |  |  |  |  |  |
| Enrolment of study children |  | X | X | X | X | X |  |  |  |  |  |  |
| Administration of IPTi drugs |  | X | X | X | X | X | X | X | X |  |  |  |
| Passive surveillance of malaria and anaemia |  | X | X | X | X | X | X | X | X | X | X |  |
| Data management |  | X | X | X | X | X | X | X | X | X | X |  |
| Interim data analysis |  |  |  |  |  |  | X |  |  |  |  |  |
| Final analysis & dissemination |  |  |  |  |  |  |  |  |  |  |  | X |

12 **Appendix 1**

The incidence of severe anaemia over the first year of life may be modelled using a deterministic compartmental model (see Figure above), with the flow between epidemiological states described by a set of linked, first order differential equations. The model is flexible, and may be modified (e.g. with additional epidemiological classes added) to better fit our biological understanding of the system.

In its simplest form, the model follows a cohort of children with a life expectancy at birth of 1/ years, where  is the underlying annual mortality rate. By a given age, all surviving cohort members are considered to be free from maternal antibodies and so susceptible to malaria infection (S0). These children acquire infection at an age-independent force of infection, λ (such that 1/ λ is the average age of first infection), thus becoming infected for the first time (I1). Once infected, they may recover (naturally or through treatment) at a rate 1 or develop severe anaemia at a rate 1. Those that recover move into the S1 class (susceptible, but having been infected once before). Those that develop severe anaemia for the first time (A1) die at a rate 1 additional to the underlying mortality rate . Those that survive move into the S1 category at a rate v1. Individuals in the S1 acquire their second infection at rate λ, enter the class I2 and, as before, may recover to the S2 category (susceptible but with two previous infections) at rate 2 or develop severe anaemia at rate 2, in which case they are subject to an additional s mortality rate. The model may be extended indefinitely, tracking the number of infections the cohort experiences. In the above example, the model is closed after three infections, by having recovery from the I3 and A3 categories to the S2 susceptible class (i.e. susceptible, but having been infected two times or more).

This model structure allows us to vary the rate at which individuals develop severe anaemia (i) or recovery without severe disease (i) as a function of the number of previous infections (i) experienced by the child. In this way, we are able to model the effects of acquired immunity in reducing the likelihood of an infected child developing severe anaemia. The model may also be extended to include variations in the parameters i and i as a function of age of the child, as well as infection history.

The effects of IPTi may be modelled by removing to a chemoprophylatically protected state, C, (not shown in above Figure) a fixed proportion, , of all the epidemiological classes at designated times, T, over the first year of life. Individuals move from the C class back into the appropriate Si categories at a rate , where 1/ is the average duration of chemoprophylaxis resulting from IPTi. The model, therefore, allows us to quantify the expected reduction in severe anaemia incidence, under different IPTi strategies (e.g. varying T and ) in different epidemiological setting (e.g. by varying ). The model can also be extended to include cerebral malarial, as well as severe anaemia, beyond the first year of life.

**Appendix 2**

**A comparative study of the efficacy of two or three doses of anti-malarial for IPTi in low transmission areas**

All IPTi studies currently under way utilise a schedule of drug administration which is very similar to that employed in the initial trial in Ifakara, Tanzania (13) with administration of the anti-malarial at the time of second DPT, third DPT and measles vaccinations, corresponding to the ages of approximately 3, 4 and 9 months. However, in low transmission areas relatively few infants will be infected with malaria before the age of about 6 months, in part because they are kept protected from exposure. In such situations, it is uncertain whether the schedule of drug administration for IPTi currently being advocated is appropriate; in such situations a two dose schedule with one dose given at the age of 4 months with DPT3 and the other at the age of 9 months with measles vaccine might be as effective as a three dose schedule, cheaper and safer.

For these reasons we propose a study in the South Pare district in which the efficacy of two and three dose regimens of the drug shown to be most effective in the present trial are compared. This would be an equivalence study with the incidence of clinical malaria during the first year of life and anaemia at the age of nine months as the main trial end-points. The study design would be similar to the one proposed in this submission and would use the same study team. However, until the first study has been completed, it is not known which would be the most appropriate drug to use for this study. Thus, investigation of this important issue has not been included in the present proposal, or budgeted for, but it is proposed as a potentially valuable continuation of investigations into the most effective ways of applying IPTi.

